### Data management and Quality control

All study data will be entered into a secure, password-protected electronic database on institutional servers. Source documents (colposcopy notes, pathology reports, case report forms) will be retained in the trial file. Data entry will be performed by the three co-investigators of the study, following a coded patient ID system to preserve confidentiality. Regular weekly encrypted backups will be retained according to institutional policy. Furthermore, data quality control will include a 10% of random cross-checks against source documents during the first 50 enrollments and thereafter regular spot-checks and automated validation rules in the database to flag missing or out-of-range values. Adverse events, protocol deviations, and biopsy/pathology discrepancies will be reviewed at monthly trial meetings, while central pathology review will resolve discordant histology. The final dataset for analysis will be locked after resolution of queries and a documented audit trail will be retained.

## Discussion

The MODUCIN1 trial is designed to evaluate whether Moducare, a plant sterol and sterolin supplement containing beta-sitosterol (BSS) and its glucoside (BSSG), can enhance the spontaneous regression of histologically confirmed low-grade cervical intraepithelial neoplasia (CIN1) compared with the standard wait-and-see approach. Based on the previous reported immunomodulatory properties of the BSS-BSSG mixture and prior clinical evidence demonstrating its efficacy in promoting clearance of HPV-associated anogenital warts [7], we anticipate that the Moducare group will demonstrate a significantly higher regression rate at six months compared to the control arm. Specifically, we hypothesize that the intervention will increase the CIN1 regression rate from the expected 60% under surveillance alone [2] to approximately 80%, representing a clinically meaningful absolute difference of 20 percentage points. If confirmed, these results would also be expected to translate into lower progression rates at both six and twelve months in the intervention arm.

The biological plausibility of this hypothesis is supported by the known mechanism of action of BSS-BSSG, which selectively enhances Th1-associated cytokines (interleukin-2, interferon-gamma) while suppressing the Th2-associated cytokine interleukin-4 [5], thereby restoring the immunological balance required for effective HPV clearance [4]. Furthermore, in vitro evidence has demonstrated that beta-sitosterol can suppress HPV E6 expression and upregulate p53 in cervical carcinoma cell lines, suggesting a direct antiviral and tumor-suppressive effect beyond immunomodulation alone [9]. Additionally, the favorable safety profile of Moducare as a natural dietary supplement justified it as a beneficial adjunct to standard surveillance.

Should the trial confirm our hypothesis, the implications for clinical practice would be substantial. Currently, the management of CIN1 relies exclusively on passive monitoring, which, despite its favorable overall natural history, leaves a clinically significant subset of patients at risk of progression, particularly those with HPV16/18-positive status, where the five-year cumulative incidence of CIN2 + can reach 25–26% [3]. The incorporation of an immunomodulatory supplement into the surveillance strategy could represent a paradigm shift in the management of low-grade cervical dysplasia, offering a non-invasive, well-tolerated intervention that actively promotes lesion regression. This approach could reduce the psychological burden associated with prolonged surveillance and decrease the need for subsequent excisional procedures.

On the other hand, some limitations of the MODUCIN1 trial should be acknowledged. The open-label design introduces the potential for performance and detection bias, as neither participants nor investigators are blinded to group allocation. While a placebo-controlled design would have been methodologically preferable, it was not feasible in the context of a dietary supplement trial where a truly inert placebo matching the appearance, taste, and dosing regimen of Moducare capsules was not available. Nevertheless, the use of an objective histological endpoint, assessed by colposcopy-directed biopsies that were centrally reviewed by the director of the Colposcopy Unit, mitigates the impact of observer bias on the primary outcome. Furthermore, the fact that pathological assessment of biopsy specimens is inherently blinded to treatment allocation provides an additional layer of objectivity.

Moreover, the six-month primary endpoint, while clinically practical and aligned with standard follow-up intervals for CIN1, may not capture the full trajectory of treatment effect, as some CIN1 lesions require longer periods for regression. The twelve-month secondary endpoint assessment partially addresses this limitation. Finally, adherence to a six-month oral supplement regimen is inherently challenging in dietary supplement trials [10], and the absence of an objective biomarker to confirm supplement intake (such as serum beta-sitosterol levels) means that treatment adherence will rely on patient self-report and capsule counting.

The dissemination plan of the study include the publication of the final results of the study in international peer-review scientific journals. Preliminary and final results may also be presented in national and international seminars and congresses relevant to colposcopy and cervical pathology.

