Endocervical curettage (ECC) is optional together with the colposcopy-directed cervical biopsies, during colposcopy at all three time points (randomization, six- and twelve-month visits) in cases with transformation zone type III. During follow-up visits pap test and HPV-DNA or RNA tests are allowed according to national and international guidelines, at the attending physician’s discretion. In case of modification in the treatment plan in either arm (Moducare dose change, participant request or disease progression to CIN3), the patient will be dropped out of the trial. The setting of the trial is a tertiary, academic center, certified by ESGO for Gynecological Oncology training, with a fully equipped Colposcopy Unit and adequate workload in order to reach the needed sample size. All patients will be treated by three gynecological oncologist, certified in colposcopy from the Hellenic Society for Colposcopy and Cervical Pathology (HSCCP) and all results will be centrally reviewed by the director of the Colposcopy Unit, who will monitor data collection (at six months after randomization), perform an interim analyses and could decide to terminate the trial. The trial has been approved by the local Scientific Committee and it is registered on clinicaltrials.gov (NCT07379905).

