### Sample size

For power analysis of the trial a two-sided alpha level of 0.05, a statistical power of 80% and accounted for a 10% drop-out rate. Based on the results of a large recent meta-analysis [2] the spontaneous regression rate of low-grade cervical intraepithelial neoplasia (CIN1) of the Wait-and-see approach was set at 60% and in order to achieve a clinically important increase of at least 20%, the regression rate of Moducare was set at 80%, since robust RCTs are absent. The sample size was calculated using RStudio (V 4.3.3), applying the chi-square test formula for comparison of two independent proportions. Accordingly, we plan to enroll approximately 182 patients to account for anticipated dropouts and maintain the integrity of the primary endpoint analysis.

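### Protection of the primary endpoint from observer bias is asserted but not secured: the director's review is not stated to be masked, and nor is the resolution of discordant histology

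*Protocol article*

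**What the plan says.** All of this is in the protocol article.

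- **Discussion, limitations.** The trial is open-label and "neither participants nor investigators are blinded to group allocation". The article acknowledges a risk of detection bias. It then says that the histological endpoint, reviewed centrally by the director of the Colposcopy Unit, lessens observer bias on the primary outcome. As an additional layer it states that "pathological assessment of biopsy specimens is inherently blinded to treatment allocation".
- **Trial design.** "all results will be centrally reviewed by the director of the Colposcopy Unit". The same sentence has the director monitor data collection, carry out interim analysis and, if so decided, terminate the trial. Nothing is said about masking this review.
- **Data management and Quality control.** "biopsy/pathology discrepancies will be reviewed at monthly trial meetings", together with adverse events and protocol deviations. The sentence goes on to assign the resolution of discordant histology to central pathology review. It does not say who performs that review, whether it is masked, or whether it comes before the meeting. A coded patient ID is already planned, for data entry and confidentiality.
- **Trial endpoints and Statistical methods.** The primary comparison is the proportion with CIN1 regression at six months, by chi-square or Fisher's exact test.

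**The concern.** In an open-label trial with a binary histological endpoint, masked outcome classification is the main available protection against detection bias. A review reduces observer bias only if the reviewer does not know the arm, or cannot alter the classification. The article claims that benefit for a reviewer who sits inside an unblinded single-centre team and who also runs the interim analyses.

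The route for discordant readings matters most, because those are the borderline cases where knowledge of the arm could tip a call. They come up at meetings that also discuss adverse events and protocol deviations, either of which can reveal the arm. If arm-aware people influence even a few such calls, part of any observed difference in regression could come from the reading rather than from Moducare. That cannot be repaired afterwards, because a reading made with knowledge of the arm cannot be made masked again.

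**Working it through.** **Step 1. Compare each claimed safeguard with the procedures.**

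| Claimed safeguard (Discussion) | What the procedures say | Does the text support it? |
|---|---|---|
| Director's central review lessens observer bias | Investigators unblinded (Discussion). The director reviews all results, does the interim analyses and can stop the trial (Trial design). No masking stated. | No |
| Pathology reading blinded by its nature | No passage says pathologists are told the arm; none says it is withheld. | Plausible for the first reading, but not secured |
| Discordance settled by central pathology review (Data management) | Discrepancies also go to monthly trial meetings. Masking, identity of the reviewer and timing are not stated. | Partly: resolution belongs to pathology, masking is open |

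Blinding is not a property of a biopsy. It depends on what the request form shows and on who talks to the pathologist.

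**Step 2. Reproduce the plan's sample size, to fix the numbers per arm.** Inputs from Sample size: "a two-sided alpha level of 0.05, a statistical power of 80% and accounted for a 10% drop-out rate"; control regression "of the Wait-and-see approach was set at 60"%; "the regression rate of Moducare was set at 80"%; "applying the chi-square test formula for comparison of two independent proportions".

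n per arm = [z(0.975)·√(2·p̄(1−p̄)) + z(0.80)·√(p1(1−p1)+p2(1−p2))]² / (p2−p1)², with p̄ = 0.70

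= [1.960·√0.42 + 0.842·√0.40]² / 0.04 = 81.2, rounded up to 82

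The total is 164, and 164/0.9 = 182.2, which agrees with the stated 182. So 182/2 = 91 per arm are randomised and about 82 per arm are expected to be evaluable. Masking does not alter this figure.

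**Step 3. Illustrate what unmasked reclassification could do.** The documents give no rate of reclassification, so the following is an assumption. There is no true effect and true regression is 60% in both arms. Between 3% and 5% of all readings in each arm are shifted, up in the Moducare arm and down in the control arm. At 91 per arm that is 0.03 × 91 = 2.7 to 0.05 × 91 = 4.6 readings per arm. The false difference is 2 × 3 = 6 points to 2 × 5 = 10 points.

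The rejection rate is the sum of the binomial probabilities of all outcome pairs for which the uncorrected chi-square statistic exceeds its 5% critical value.

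| False difference | Rates compared | 91 per arm | 82 per arm |
|---|---|---|---|
| 0 points | 60% v 60% | 5.1% | 4.8% |
| 6 points | 57% v 63% | 13.2% | 11.8% |
| 10 points | 55% v 65% | 28.2% | 25.1% |

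Check by normal approximation at 91 per arm for 6 points: SE under the null = √(2·0.24/91) = 0.0726, so the critical difference is 1.960 × 0.0726 = 0.1423. SE under the shift = √((0.2451+0.2331)/91) = 0.0725. Then Φ((0.06−0.1423)/0.0725) + Φ((−0.06−0.1423)/0.0725) = 0.128 + 0.003 = 0.131, in line with 13.2%.

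**The case against.** The strongest reply has five parts.

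1. **A reader might infer that protection from observer bias is absent. The documents do not support that.** No passage says that pathologists know the arm, belong to the investigator team or see the allocation list. The first reading may well be masked in practice. This stands.
2. **A reader might infer that the monthly meeting decides discordant cases.** It does not: central pathology review resolves them. This stands. What remains open is whether that review is masked and whether it is recorded before the meeting.
3. **A reader might infer that the director is known to be unmasked and can overrule pathology.** Neither is stated. Knowledge of the arm is a strong inference from the open-label design and the interim role. Power to change a reading is not described at all, and the role may be no more than oversight. This stands, but it cuts both ways: a review that is only oversight cannot be credited with reducing observer bias either.
4. **Specimen labelling and pathology workflow are details that an article leaves to the full protocol.** This is fair, and the missing labelling procedure is not the point here. The point is that the article states a safeguard in the director's review that its own procedures do not support.
5. **The article already discloses detection bias and claims only to reduce it.** True, but that reduction is the claim that lacks support where the director's review is concerned.

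The size of the illustrated shift has no source in the documents, and a shift directed by arm presupposes unmasked reclassification. It shows sensitivity, not an expected bias.

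**Conclusion.** The concern holds in this form: protection of the primary endpoint is asserted but not secured. The director's review, as described, cannot count as a safeguard against observer bias. Blinding of pathology is plausible but rests on a statement rather than an arrangement, and it is least certain for discordant readings.

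No figure in the plan is wrong on this account, and the stated 182 reproduces. The potential size is given only by the illustration: roughly three to five readings per arm moved in opposite directions would raise the false-positive rate from 5% to between about 12% and 28%, depending on the shift and the number evaluable. That rests on the assumed shift, no true effect and 60% regression. The conclusion about the director's review does not depend on those numbers. It does rest on reading the director as part of the unblinded team, which is an inference.

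This should be corrected before enrolment, which is planned from 01/06/2026.

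**What to change.** 1. Define the primary endpoint as the pathology report on specimens and request forms that carry the existing coded ID and no arm or supplement information.
2. State that central pathology review resolves discordant histology masked to arm, and that the result is recorded before the case is raised at any trial meeting.
3. Limit the director's outcome review to completeness, or carry it out on reports with the arm removed. Keep it separate from the interim analysis.
4. In the Discussion, replace the statement that pathology is blinded by nature with a description of these steps. Delete or qualify the statement that the director's review lessens observer bias.
5. Keep as a stated limitation that unblinded colposcopists judge which areas are suspicious and take the biopsies, including from newly suspicious quartiles at follow-up (Trial design). Masked reading does not remove bias at that stage.

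The cost is minor labelling and workflow wording, using the coded ID and the central pathology review already planned. No extra reader and no extra patients are needed. The director gives up unmasked review of outcomes.

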### Statement of ethics

This clinical trial protocol was approved by the Institutional Review Board of “Papageorgiou” General Hospital (no. 2025-Β2015–518, date: 14/01/2026). For any protocol amendment a new approval will be obtained Institutional Review Board. The study will be conducted according to the Declaration of Helsinki and all potential study participants will be given a written informed consent before enrolment. Patients’ data will be available upon request from the corresponding author for the reproducibility of this study.
